## **2.4 Eligibility Criteria**

### **2.4.1 Inclusion criteria**

Patients are eligible if they are 55 years or older AND meet any one of the following criteria:

1. have stage II-IV ovarian or endometrial cancer, undergoing cytoreductive surgery via laparotomy, with or without NACT
2. have any stage endometrial, uterine or cervical cancer planned for laparotomy where laparoscopy is deemed unfeasible/high-risk due to comorbidities
3. are undergoing laparotomy for pelvic mass, highly suspicious for malignancy; or
4. are undergoing laparotomy for gynecologic malignancy recurrence.

### **2.4.2 Exclusion criteria**

Patients are ineligible if they meet any one of the following criteria:

1. are unable to provide informed consent
2. require urgent surgery within 24 hours of first consultation to the GO team
3. are undergoing neoadjuvant radiation therapy
4. have a previously documented history of dementia
5. have cognitive, language, vision, or hearing impairment that impacts ability to understand the directions for the completion of the study instruments
6. are participating in a clinical trial investigating a new systemic therapy

## **2.5 Patient Recruitment Plan and Informed Consent**

At least 3 centres will participate in the FARGO study. Research personnel will screen the list of patients aged 55 years or older, diagnosed with a suspected or confirmed gynecologic malignancy and requiring a) a surgical intervention performed by laparotomy or b) NACT, with plan for interval surgery via laparotomy, who are scheduled for any pre-operative or pre-chemotherapy visit at the participating centres. Clinics involved in the pre-operative or pre-chemotherapy assessment of the potential study population as per local practice (e.g. GO clinics, internal medicine clinics, anesthesiology clinics, etc.) will be engaged in the patient screening process. If a patient meets the criteria, study personnel will approach the patient to obtain their informed consent.

## 2.6 Registration

Registration will occur immediately after a patient is deemed eligible and informed consent is obtained. For patients who are not receiving chemotherapy before surgery, registration should occur within 45 days prior to their surgery. For patients who are receiving chemotherapy before surgery, registration should occur within 30 days prior to their first chemotherapy treatment. Research personnel will register patients via a password protected Interactive Web Registration System (IWRS). The IWRS is a 24-hour computerized registration internet system maintained by the coordinating centre at the PHRI, which is part of Hamilton Health Sciences and McMaster University in Hamilton, Ontario, Canada.

## 2.7 Study flow

Figure 1 shows the FARGO patient flow diagram. We expect that some of the eligible patients (group A) will undergo surgery without NACT. Group A will undergo only one preoperative study visit (baseline) within 45 days prior to their surgery. Patients undergoing NACT before their surgery (group B) will have a first baseline study assessment within 30 days prior to their first chemotherapy treatment; in this group, a second preoperative study visit will be repeated after chemotherapy is considered terminated at least 18 days post-chemotherapy cycle and within 45 days prior to surgery. Post-chemotherapy, a small proportion of patients will not be deemed eligible for surgery by the treating physician (group C). Group C will be only included in the evaluation of chemotherapy-related outcomes and then will leave the study. Group A and B will complete the study assessments and follow-ups. Some patients of group A and group B will undergo adjuvant chemotherapy after surgery; this will not affect their study timeline.

## 3. MAIN STUDY PREDICTORS (EXPOSURES)

### 3.1 Assessments

We will assess every patient enrolled upon the following predictors.

#### 3.1.1 *Frailty Phenotype*

Frailty will be measured based on the FP evaluation. The FP assessment is based on the following 5 criteria: weak muscle strength (decreased grip strength measured with a dynamometer), slow gait speed (measured on the 15-ft walking test), unintentional weight loss (> 10 lbs), exhaustion (self-reported), and low physical activity (low weekly energy expenditure). The patient receives 1 point for each criterion met, for a total score of: 0 to 1, not frail; 2 to 3, intermediate frail (pre-frail); 4 to 5, frail. The frailty status based on these categories will be evaluated as exposure for the primary research question. The actual FP score (i.e., from 0 to 5) and the score upon each of the components of the FP assessment will be secondarily evaluated as exposures/predictors. With an exploratory intent, at the first study FP assessment, the level of physical activity will be evaluated with regards to two different time point, i.e., the current level (which is what will enter the FP scoring for the purpose of the study objectives), and the usual level (before the diagnosis of cancer was made, or before the cancer likely started affecting their performance and lifestyle).

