### **1.2.3 Age-related frailty**

Frailty is being increasingly studied as predictor of adverse outcomes. Frailty is a multidimensional geriatric syndrome characterized by increased vulnerability to stressors as a result of reduced capacity of different physiological systems. Cumulative evidence has associated frailty with an increased risk of adverse health-related outcomes including falls, disability, hospitalizations and mortality. In patients who undergo surgery, Frailty is associated with increased short-term morbidity, including falls, disability, increased resource utilization, and 1-year mortality after surgery. In patients living with cancer, frailty may also independently predict oncologic outcomes and treatment tolerance. Several ways of operationalizing this concept have been proposed, without reaching a formal consensus. Two aspects, however, are common across different frailty definitions. First, they have been consistently associated with adverse outcomes. Second, although frailty is often described as being present or absent, frailty indexes or scales can be used to grade a condition with higher levels of frailty being associated with greater vulnerability and risk of adverse outcomes.

The most commonly used definition of frailty was developed by Fried et al. as part of their work in the Cardiovascular health study and the Women's Health and Aging Studies. It has a focus on the physical domain and it is known as Physical Frailty or FP. According to this definition, frailty corresponds to a condition meeting at least 3 out of 5 criteria, including weak muscle strength, slow gait speed, unintentional weight loss, exhaustion, and low physical activity.

Many investigators have suggested a broader multidomain framework for frailty. According to the accumulating deficit model, for example, frailty is measured as an index obtained by counting the number of deficits present across multiple domains ( $\geq 30$  deficits must be assessed).

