### 3.1.3 Cognitive frailty

We will study the predictive performance of cognitive frailty based on the I.A.N.A./I.A.G.G. definition, and combining the FP with the MoCA in order to classify patients into the 4 categories of 1) robust older individuals (i.e., no evidence of physical frailty) without cognitive problems (i.e., normal brain aging); physically frail older adults ( $FP \geq 4$ ) with normal cognitive functioning ( $MoCA \geq 26$ ); 3) older adults with no physical frailty ( $FP < 4$ ) but already exhibiting a cognitive impairment ( $MoCA < 26$ ); 4) physically frail older adults ( $FP > 04$ ) with cognitive impairment ( $MoCA < 26$ ).

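### The primary frailty exposure classes a score of 3 as pre-frail, although the protocol's own description of the Frailty Phenotype, citing the same reference, calls it frail

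*Protocol*

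**What the plan says.** Protocol section 1.2.3 (Age-related frailty) introduces the FP, cites reference 29, lists five criteria (grip strength, gait speed, weight loss, exhaustion, physical activity) and states that "frailty corresponds to a condition meeting at least 3 out of 5 criteria". It gives no limits for a pre-frail group.

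Section 3.1.1 (Frailty Phenotype) opens with "Frailty will be measured based on the FP evaluation. 29" and lists the same five criteria at one point each. It then classifies the total as "0 to 1, not frail; 2 to 3, intermediate frail (pre-frail); 4 to 5, frail". On the role of these groups it says: "The frailty status based on these categories will be evaluated as exposure for the primary research question". The ungrouped score is given a lesser role: "The actual FP score (i.e., from 0 to 5) and the score upon each of the components of the FP assessment will be secondarily evaluated".

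Section 6.1 (Primary Analysis) fits one logistic model with frailty as predictor and one with RCRI+age+MINS, and compares their c-statistics.

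Section 3.1.3 (Cognitive frailty) crosses the FP with the MoCA. Its second group needs FP of 4 or more with MoCA of 26 or more, and its third needs FP below 4 with MoCA below 26. Its fourth is printed as "physically frail older adults ( $FP > 04$ ) with cognitive impairment".

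**The concern.** The two sections describe the same instrument, with the same criteria and the same source, and set different frail thresholds. The disputed patients are those with a score of 3. The conflict sits in the sole predictor of one of the two models in the primary comparison. The primary objective and research question name the FP without qualification, so a reader of the results would assume the definition in section 1.2.3, while the analysis would use a stricter one.

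Two things are at stake. One is what the primary result is a result about. The other is that a protocol containing two thresholds leaves room to choose between them after the data are seen. A statistical analysis plan could settle the choice only by overriding one of the two statements.

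**Working it through.** **1. The two definitions, score by score.**

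| FP score | Section 1.2.3 | Section 3.1.1 |
|---|---|---|
| 0, 1 | not frail | not frail |
| 2 | not frail | pre-frail |
| 3 | frail | pre-frail |
| 4, 5 | frail | frail |

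Frail status differs at score 3 only. Section 1.2.3 sets no pre-frail limit, so the rows for 0 to 2 show no conflict.

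**2. How many patients this could concern.** The protocol gives no FP distribution. Assume the score is Binomial(5, q). Then P(3) = 10q³(1−q)² and P(≥4) = 5q⁴(1−q) + q⁵.

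| q | P(3) | P(≥4) | P(≥3) | Frail of 280, cut ≥4 | Frail of 280, cut ≥3 |
|---|---|---|---|---|---|
| 0.2 | 0.051 | 0.007 | 0.058 | 2 | 16 |
| 0.3 | 0.132 | 0.031 | 0.163 | 9 | 46 |
| 0.4 | 0.230 | 0.087 | 0.317 | 24 | 89 |

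At q = 0.3, for example, P(3) = 10 × 0.027 × 0.49 = 0.132.

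**3. The sample size does not use the cut.** Appendix I compares two AUCs with 20% events, correlation 0.5 and two-sided alpha 0.05. I used the Hanley-McNeil variance, with the null variance taken at the lower AUC. For 0.60 against 0.73 at N = 250 (50 events, 200 non-events), the variances are 0.00215 and 0.00188. The variance of the difference is 0.00215 + 0.00188 − √(0.00215 × 0.00188) = 0.00202, and the null variance is 0.00215. Then (0.13 − 1.96 × 0.0464)/0.0449 = 0.87, above the 0.84 needed for 80% power. N = 245 just misses, so 250 is reproduced. Allowing for 10% loss, 250/0.9 = 278, in line with 280. No FP threshold enters.

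**4. What grouping does to the AUC.** Assume a normal latent frailty variable with AUC 0.68 and 20% events. The shift between patients with and without the outcome is d = √2 × Φ⁻¹(0.68) = 0.661. Cut points x solve 0.2Φ(x − d) + 0.8Φ(x) = cumulative share of the score. With P_i and N_i the shares of patients with and without the outcome in group i, AUC = Σ P_i (Σ_{j<i} N_j + N_i/2).

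Example, q = 0.3, protocol groups: P = (0.323, 0.599, 0.078), N = (0.580, 0.401, 0.019). AUC = 0.323 × 0.290 + 0.599 × 0.7805 + 0.078 × 0.9905 = 0.638 (0.639 unrounded).

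| Assumed distribution | 0-5 score | 0-1 / 2-3 / 4-5 | 0-1 / 2 / 3-5 | 0 / 1-2 / 3-5 |
|---|---|---|---|---|
| q = 0.2 | 0.662 | 0.619 | 0.623 | 0.631 |
| q = 0.3 | 0.667 | 0.639 | 0.652 | 0.633 |
| q = 0.4 | 0.668 | 0.640 | 0.655 | 0.638 |
| Shares 15, 25, 25, 18, 11, 6% | 0.673 | 0.655 | 0.652 | 0.647 |

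The 0-5 score keeps about 0.66 to 0.67. Every three-level grouping loses some discrimination, and none is best throughout. The loss therefore comes from collapsing the score, not from placing the frail cut at 4 rather than 3. A separate illustration, with logistic risk and an odds ratio of 1.5 to 2.0 per point over q = 0.2 to 0.4, agrees. Moving only the frail cut (0-1/2-3/4-5 to 0-1/2/3-5) changes the AUC by 0.003 (0.572 to 0.575) to 0.020 (0.660 to 0.680).

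**5. The cognitive-frailty groups.** There are 12 cells: FP 0 to 5 by MoCA below 26 or not. Group 1 has no printed FP or MoCA limit; read it as FP below 4 with MoCA of 26 or more. Taken literally, FP = 4 with MoCA below 26 falls in no group, and the other 11 cells are each covered once. With FP of 4 or more in group 4, all 12 are covered once.

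**The case against.** The best defence is that section 1.2.3 is background and section 3.1.1 is the operating rule. Section 3.1.1 is explicit, and 3.1.3 uses the same threshold of 4, which is compatible with a deliberate choice. Section 1.2.3 itself says that no formal consensus exists on how to operationalise frailty and that frailty can be graded. A categorical exposure also matches the categorical comparator in sections 3.1.4 and 3.1.5, and the 0-5 score is already prespecified as a secondary predictor.

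Much of this stands. An analyst following 3.1.1 would know what to program, and preferring the 0-5 score is a modelling judgement rather than the correction of an error. It does not remove the contradiction: 3.1.1 presents its measure as the FP of reference 29, gives no sign of a modification, and disagrees with the protocol's own account of that definition.

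A reader might infer more than the documents support:

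- **That the study is underpowered.** In Appendix I, 80% power against 0.55 needs 240 patients at AUC 0.68 and 405 at 0.65, so a grouping loss might seem to force that step. But section 2.3 assumes 0.68 for the FP model itself, not for a latent variable from which a loss must be deducted. The loss is also not caused by the disputed cut.
- **That calling scores 0-1 not frail is wrong**, or that the lower groups should be 0 and 1-2. Section 1.2.3 gives no pre-frail limit.
- **That the result cannot be compared with the study cited for the 0.68.** The protocol does not state that study's frailty cut-offs.
- **That the gap in 3.1.3 is a design flaw.** The printed threshold is malformed, and the neighbouring groups make the intended complement plain. It is almost certainly a misprint for 4 or more and touches one secondary objective.

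**Conclusion.** The point holds as an internal contradiction in the definition of the primary exposure, and it should be resolved before analysis. It rests on the protocol's text alone and concerns patients with a score of exactly 3. Its size cannot be known from the document. Under the Binomial assumption, 5% to 23% of patients would be classified differently, and at the low end the 4-5 group would hold only about two patients. The effect of the cut itself on the AUC is small and of uncertain direction.

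The case for the 0-5 score is secondary. It rests on the assumed distributions and on a latent AUC of 0.68, with about 0.66 to 0.67 retained against about 0.62 to 0.65 for the protocol's three groups. The malformed threshold in 3.1.3 is a minor correction.

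**What to change.** 1. Reconcile sections 1.2.3, 3.1.1 and 3.1.3 before analysis. Either use at least 3 of 5 as the frail threshold in 3.1.1 and 3.1.3, as in the cited definition, or state in 3.1.1 that 4-5 is a deliberate modification, justify it, and prespecify the at-least-3 classification as a sensitivity analysis of the primary comparison.
2. Consider making the 0-5 score the primary predictor in section 6.1, with the categories secondary. This frees the primary c-statistic from the disputed cut. The downside is small: a linear or ordinal assumption for the score.
3. In section 3.1.3, give group 4 the same FP threshold as group 2, and print the limits for group 1, so that the four groups cover every patient once.

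The cost is wording in 3.1.1, 3.1.3 and, if item 2 is adopted, 6.1. The item-level FP data are already collected, so no visit, assessment or sample-size figure changes.

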### 3.1.2 Clinical Frailty Scale

Frailty will be also assessed using the Clinical Frailty Scale (CFS). The CFS is a global frailty scale according to which the patient is assigned a category from 1 (“Very fit”) to 9 (“Terminally ill”), as a summative clinical judgment; frailty is present if a category  $\geq 4$  is assigned. Depending on the study objective, the FP-based or CFS-based assessment will enter the predictive models either as preoperative baseline (static) variable only, or as a dynamic predictor obtained by a repeated postoperative assessment to reflect the impact of NACT, when applicable (i.e., change in frailty from before to after NACT but before surgery); and the impact of surgery (i.e., change in frailty from preoperative to 28 days after surgery).

### 3.1.3 Cognitive frailty

We will study the predictive performance of cognitive frailty based on the I.A.N.A./I.A.G.G. definition, and combining the FP with the MoCA in order to classify patients into the 4 categories of 1) robust older individuals (i.e., no evidence of physical frailty) without cognitive problems (i.e., normal brain aging); physically frail older adults ( $FP \geq 4$ ) with normal cognitive functioning ( $MoCA \geq 26$ ); 3) older adults with no physical frailty ( $FP < 4$ ) but already exhibiting a cognitive impairment ( $MoCA < 26$ ); 4) physically frail older adults ( $FP > 04$ ) with cognitive impairment ( $MoCA < 26$ ).

### 3.1.4 Revised Cardiac Risk Index (RCRI) and age

Based on the collection of data on the past medical history at the time of undergoing surgery and on the type of surgery, each participant will have a preoperative RCRI calculated. The RCRI includes 6 factors, each worth 1 point (i.e., history of ischemic heart disease, cerebrovascular disease, congestive heart failure, preoperative insulin use, preoperative creatinine  $> 177$  mmol/L, and high-risk surgery). For the purpose of the primary research question, each participant will be classified as being at high risk if their  $RCRI \geq 1$ , or if the RCRI is 0 but they are 65 years old or older. Secondly, the predictive performance of the RCRI as a 0-to-6 score (combined or not with age) will be evaluated.

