### ***1.2.2 Current perioperative risk assessment in gynecologic oncologic patients and its limitations***

In current practice, decisions regarding surgery and chemotherapy candidacy are initially made by the treating gynecologic oncologist based on a subjective judgement of the expected treatment tolerance, based on a non-systematic assessment of patient performance status, and most often influenced by the patient chronologic age. When a patient is deemed to be a probable surgical candidate, anesthesia, internal medicine, cardiology, and/or perioperative medicine consultants are often involved, based on patient age and/or presence of comorbidities, to finalize the decision about surgery and optimize the perioperative risk management. Cardiovascular risk assessment often plays a major role in this perioperative risk evaluation.

The RCRI is currently the most validated index among the clinical risk indexes for preoperative cardiac risk assessment. The RCRI includes 6 factors, each worth 1 point (i.e., history of ischemic heart disease, cerebrovascular disease, congestive heart failure, preoperative insulin use, preoperative creatinine > 177 mmol/L, and high-risk surgery). In a systematic review that included 792,740 patients from 24 studies, the RCRI showed moderate discrimination to predict major perioperative cardiac complications. The Canadian Cardiovascular Society Guidelines on Perioperative Cardiac Risk Assessment and Management for Patients Who Undergo Noncardiac Surgery suggest clinicians use the RCRI over the other available clinical risk prediction scores (Conditional Recommendation; Low-Quality Evidence). These guidelines also provide updated pooled risk estimates obtained from external validation studies of the RCRI that were published in the past 15 years, in which perioperative troponin was systematically monitored.

The VISION study, a prospective cohort study of 40,000 patients aged ≥45 years-old undergoing noncardiac surgery worldwide, has showed that MINS, defined as a postoperative troponin elevation judged to be due to myocardial ischemia, with or without symptoms or electrocardiogram

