## 2.2 Study Design

This is a multicentre prospective cohort study of patients 55 years old or older with confirmed or suspected gynecologic cancer who are candidates to cytoreductive or high-risk surgery (laparotomy) with or without chemotherapy at centres.

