## **6. STATISTICAL ANALYSES**

### **6.1 Primary Analysis**

The primary analysis will compare the performance of preoperative frailty assessment based on the FP and perioperative cardiovascular risk assessment based on the combination of preoperative RCRI, age and occurrence of MINS, in predicting the composite of all-cause death or new disability at 6 months after surgery. We will assess the association of FP and of RCRI+age+MINS with the primary outcome using logistic regression models. We will perform one logistic regression model including frailty as predictor, and one logistic regression model including the baseline RCRI+age+MINS as predictors. For each model we will then calculate the c-statistics (corresponding to the AUROC) and compare them using a non-parametric approach. We will include in the primary analysis only study participants who are alive at 28 days after surgery. We expect this will exclude from the primary analysis a very small proportion of patients initially enrolled in the study (i.e.,  $\leq 2\%$ ). We will initially exclude from the primary analysis those patients for whom postoperative troponin measurement was

not performed (for reasons other than death); as a sensitivity analysis, these patients will be then included and considered as not having MINS. For the primary analysis we will not include other covariates in the regression models. We will secondarily include the type of gynecological diagnosis/indication (based on our inclusion criteria) as covariate and as effect modifier.

As part of our secondary objectives, we will also evaluate the utility of frailty *when added* to the RCRI+age+MINS as predictors by calculating the net absolute reclassification improvement.

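### The RCRI renal criterion is printed as creatinine above 177 mmol/L, which no patient can reach; as written the renal point is always 0, mainly affecting the secondary 0-to-6 score analyses

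*Protocol*

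**What the plan says.** Section 3.1.4 is where the protocol fixes how each participant's RCRI is calculated. It states "The RCRI includes 6 factors, each worth 1 point", and the last two factors in its list are "preoperative creatinine $> 177$ mmol/L, and high-risk surgery". The background text in section 1.2.2 gives the same list and the same unit: "preoperative creatinine > 177 mmol/L, and high-risk surgery". No other section gives a different unit, a conversion or a correction.

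The index is used in two ways:

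- **Primary question.** Section 3.1.4 classes a participant as high risk if the RCRI is at least 1, "or if the RCRI is 0 but they are 65 years old or older". Section 3.1.5 then requires MINS as well: only a high-risk participant who has MINS counts as exposed, and everyone else is low risk. Section 6.1 describes the comparator as "one logistic regression model including the baseline RCRI+age+MINS as predictors".
- **Secondary use.** Section 3.1.4 adds that "the predictive performance of the RCRI as a 0-to-6 score (combined or not with age) will be evaluated".

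The study surgery bears on a different RCRI factor. Section 2.2 describes participants as "candidates to cytoreductive or high-risk surgery (laparotomy) with or without chemotherapy", while high-risk surgery is itself one of the six factors and the protocol does not define it.

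**The concern.** The cut-off appears to carry the wrong unit by a factor of 1,000. It stands in the definition of a predictor, not only in background prose, so it is the rule from which a form, a range check or a scoring program would be built. If the printed rule were coded literally, no participant could score the renal item. The section would then contradict itself, because six one-point factors are meant to give a maximum of 6 and one of them could never be met. The loss would fall on participants with renal impairment, and only on the cardiovascular index, not on the frailty measures it is compared with.

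**Working it through.** The cut-off is a definition, not a derived figure, so there is no calculation in the plan to reproduce. The check is a unit conversion, followed by tracing which analyses use the renal point.

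**Step 1: conversion.** Inputs: 177 mmol/L (sections 3.1.4 and 1.2.2) and the molar mass of creatinine, C4H7N3O.

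- Molar mass = 4 × 12.011 + 7 × 1.008 + 3 × 14.007 + 15.999 = 113.12 g/mol.
- As printed: 0.177 mol/L × 113.12 g/mol = 20.0 g/L = 2,002 mg/dL.
- Same number in micromol/L: 0.000177 mol/L × 113.12 g/mol = 0.0200 g/L = 2.0 mg/dL.

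**Step 2: can the printed value be reached?** Take 1 to 3 mmol/L as an assumed range of extreme blood creatinine. The printed cut-off is 177/1 = 177 times the lower end and 177/3 = 59 times the upper end. No plausible choice of extreme makes the criterion attainable.

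**Step 3: effect on the score.** With the renal item fixed at 0, the maximum is 6 − 1 = 5. Each participant above the intended cut-off scores one point too low. The documents do not give that share. At an assumed 1% to 5% of 280 it would be 2.8 to 14 participants.

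**Step 4: effect on the primary category.** Under sections 3.1.4 and 3.1.5, exposed means (RCRI ≥ 1, or RCRI 0 and age ≥ 65) and MINS. Consider a participant whose true renal point is lost:

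| Participant | Category if renal point lost |
|---|---|
| Age 65 or older | Unchanged: high risk by age even at RCRI 0 |
| Under 65, another RCRI factor present | Unchanged: RCRI still ≥ 1 |
| Under 65, no other factor, no MINS | Unchanged: low risk either way |
| Under 65, no other factor, MINS | Changes from exposed to not exposed |

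Only the last row matters. For illustration, with every input assumed and treated as independent:

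- Low: 280 × 1% renal × 30% under 65 with no other factor × 10% MINS = 0.084, about 0.1 participant.
- High: 280 × 5% × 50% × 20% = 1.4 participants.

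If every study laparotomy earns the high-risk-surgery point, RCRI ≥ 1 holds for all, the last row is empty and the effect is exactly zero.

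**Step 5: sample size.** Section 2.3 and Appendix I rest on the assumed AUCs, a 20% outcome rate and a correlation of 0.5. None of these uses the creatinine cut-off, so the 250 and 280 stand.

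**The case against.** **It may be a reading artefact.** The error is a single character, and the text was extracted by a program from a PDF. No micro sign appears elsewhere in the supplied text to show that one would have survived, and the two sentences are near copies. This stands as a caveat. It is weakened, but not removed, by the two places having been rendered differently (one as a mathematical expression, one as plain text) and still agreeing on the unit.

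**The harm may never occur.** If sites enter the number their laboratory reports in micromol/L and the program compares it with 177, the item scores correctly despite the label. Section 9.1 plans range checks, data validation and monitoring for outliers, and section 3.1.4 cites the publication behind the index. This too stands: the form, the scoring program and the Manual of Operations are not at hand, and nothing shows that they carry the wrong unit. A reader might infer that centres will score the item differently from one another, but the protocol gives no evidence of that.

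**The primary comparison is hardly touched.** A reader might infer that the error weakens the cardiovascular comparator and so favours frailty in the primary analysis. The documents do not support this. The comparator is dichotomised and also requires MINS, so the renal point can move only the narrow group in the last row of the table, and possibly nobody. Nor should the 2.8 to 14 participants be read as reclassified: they are those who would lose a score point under an assumed prevalence.

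None of these arguments makes the printed cut-off attainable.

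**Conclusion.** The point holds as an error in a predictor definition with limited consequences. The printed threshold is 1,000 times the only plausible reading of the same number. Taken literally it makes the renal point unattainable and caps the score at 5. The consequence lies in the secondary analyses of the RCRI as a score, where each participant above the intended cut-off is one point too low; how many that is cannot be known from the protocol. The primary comparator changes little or not at all, and sample size and power do not change.

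This rests on three assumptions: that the extracted text matches the source file; that the rule would be applied as printed; and that the primary comparator is the combined category of section 3.1.5. If section 6.1 instead means that the RCRI-and-age class and MINS enter as separate terms, the MINS condition drops out, but only participants under 65 with no other RCRI factor could still be affected.

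**What to change.** Confirm the unit in the source file and against the publication cited for the index (reference 49), then correct it to micromol/L in sections 3.1.4 and 1.2.2. Check that the data collection form, range checks, scoring program and Manual of Operations all use that unit. If any RCRI values have already been derived by program, rerun the renal item from the recorded creatinine. The cost is one unit symbol in two places and a short check of the scoring. No design element, sample size or analysis model has to change.
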